**4.2. Description of the study methodology****Study scheme (Figure 1)**

The tolerance study will be carried out by adapting the 2-step scheme of Simon (Simon, 1989) initially, and then by carrying out an increase in doses if tolerance is satisfactory.

From the data in the literature, it appears that the frequency of intolerance to treatment is <7% for a dose of 25 mg/day and <10% for a dose of 50 mg/day, which seems acceptable in this population and leads us to envisage a subsequent therapeutic trial. Conversely, its use does not appear possible if the respective frequencies are >15% and 20%, respectively.

In these conditions, for this tolerance study, we proposed a scheme which includes three successive stages combining the plan of Simon in two stages at a dose of 25 mg/day, and then an increase in dose to 50 mg/day with evaluation at a single time (Figure 1).

Under these conditions, the risk of not revealing unacceptable tolerance of eplerenone in this population is <10% and the risk of deciding, if tolerance permits, to not use it is 27%. There is a 60% chance of interrupting the study before the increase in dose if the hypothesis of unfavourable treatment is correct.

The advantages of the study scheme are that it will demonstrate unacceptable toxicity as early as possible and will detect a possible threshold effect between the doses of 25 mg/day and 50 mg/day which will allow the use of the lowest dose possible.

**Step 1:** 14 patients will be included in the first step, at an eplerenone dose of 25 mg/day. This stage will last 8 weeks. If  $\geq 3$  adverse events requiring the termination of treatment occur during these 8 weeks, the study will be stopped and the treatment will be considered to be too poorly tolerated to be used in this population. If <3 adverse events occur, we will proceed to step 2.

**Step 2:** This will consist of the addition of an additional 17 patients. All of the patients (14+17) will be treated with eplerenone at a dose of 25 mg/day for 8 weeks. If >4 adverse events requiring the termination of treatment occur during the 8 weeks, the study will be stopped and the treatment will be considered to be too poorly tolerated to be used in this population. If  $\leq 4$  adverse events occur, we will proceed to step 3.

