**Step 3:** This will consist of an increase in the dose of eplerenone to 50 mg/day in all patients who participated in step 2. The duration of this step will be 8 weeks. If  $\geq 5$  adverse events requiring the termination of treatment occur, the study will be stopped and the treatment will be considered to be too poorly tolerated to be used in this population. If  $\leq 4$  adverse events occur, the tolerance of eplerenone treatment in this population will be considered to be acceptable.

[figure not shown]

**Figure 1. Study scheme** showing the different possibilities

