#### **5.3.1 Criteria and modalities for the premature termination of treatment or exclusion of a subject from the study**

A patient participating in the study leaves the study when they:

- 1) present with at least one of the adverse event criteria requiring the cessation of eplerenone treatment:
  - hyperkalaemia  $\geq 6$  mmol/L and/or hyperkalaemia  $\geq 5.5$  mmol/L under 2 spoon-measures/day of KAYEXALATE®
  - acidosis revealed by an alkaline reserve of  $\leq 15$  mmol/L
  - systemic arterial hypotension revealed by a systolic arterial pressure  $< 100$  mmHg
  - orthostatic hypotension defined by a decrease in systolic arterial pressure of  $> 20$  mmHg in the 3 minutes following standing
  - acute renal failure defined by an increase in creatininaemia of  $> 30\%$  in comparison with its value at inclusion
  - all other unexpected adverse events requiring the termination of eplerenone treatment
- 2) present with an indication for treatment that is contraindicated in association with eplerenone (trimethopim, digoxin ...)

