### 9.3. Size of the sample / population

#### 9.3.1 Calculation and/or justification of the number of subjects required

##### 9.3.1.1. Baseline hypothese(s) for this calculation:

According to data in the literature, the probabilities of hyperkalaemia developing during 8 weeks of eplerenone treatment are <7% with the 25 mg dose and <10% with the 50 mg dose (Gonzalez Monte *et al.*, 2010, Pitt *et al.*, 2003, Pitt *et al.*, 1999, Zannad *et al.*). We posed the alternative hypothesis that it is not useful to continue the study if the risk of hyperkalaemia is >15% with the 25 mg dose and 20% with the 50 mg dose.

The power for detecting an adverse event requiring the termination of treatment was fixed at 90%.

Under these hypotheses, it is possible to carry out a study in several steps by adapting the 2-step scheme proposed by Simon (Simon, 1989) in the following way:

First step: 14 patients will be included at the dose of 25 mg and followed for 8 weeks: if  $\geq 4$  patients experience an adverse event requiring the termination of treatment, the study will be stopped. In the opposite case, 17 additional patients will be included at the same dose for 8 weeks. If  $\geq 5$  patients out of the 31 have a limiting toxicity, the alternative hypothesis can be rejected and the study will be stopped; in the opposite case, the dose will be increased to 50 mg for 31 patients with a follow-up at 6 months. If at the end of this follow-up,  $\leq 4$  patients have a limiting toxicity with the 50 mg dose, the alternative hypothesis will be rejected and continuation of the study with eplerenone will be possible.

In these conditions, the probability of demonstrating a limiting toxicity greater than the fixed norms is 90.0%, the risk of stopping the study wrongly is 27.6%.

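### Section 4.2 words the three stopping rules in adverse events and section 9.3.1.1 words them in patients; the stated 27.6% and 90.0% hold only for one count per patient, with the step 1 limit of 3 printed in 4.2

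*Protocol*

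**What the plan says.** Section 4.2 sets the decision rules. For step 1, "14 patients will be included in the first step, at an eplerenone dose of 25 mg/day". At three or more, "adverse events requiring the termination of treatment occur during these 8 weeks, the study will be stopped"; below that, "If <3 adverse events occur, we will proceed to step 2". Step 2 stops at more than four events among 31 patients. Step 3 has the same form: at five or more, "adverse events requiring the termination of treatment occur, the study will be stopped". The unit is the event in all three steps. Section 4.6.2 refers back to section 4.2 for the end of the study, and section 9.1 does so for the primary analysis, so these are the operative rules.

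Section 9.3.1.1 states the same scheme in patients. In the first step, with four or more, "patients experience an adverse event requiring the termination of treatment, the study will be stopped". Otherwise "17 additional patients will be included at the same dose for 8 weeks", and with five or more, "patients out of the 31 have a limiting toxicity, the alternative hypothesis can be rejected and the study will be stopped". Four or fewer patients with limiting toxicity at 50 mg is acceptable. The section then gives a 90.0% probability of showing excessive toxicity and a 27.6% risk of stopping wrongly.

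Section 5.3.1 has a patient leave when they "present with at least one of the adverse event criteria requiring the cessation of eplerenone treatment". Sections 4.6 and 4.6.1 make that exit permanent. Section 4.1 lists the criteria separately; systolic pressure below 100 mmHg and an orthostatic fall of more than 20 mmHg are two entries.

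**The concern.** A stopping rule needs one unit, and here the operative text and the text that carries the error rates use different ones. Permanent exit prevents a patient from adding events over time. It does not settle what happens when two listed criteria are met at the same assessment. Both hypotension criteria come from one blood pressure examination, and Tables 1 and 2 place potassium, renal function and blood pressure together at D14, D28 and D56 (D28 and D56 only for group A in step 2). Someone applying section 4.2 literally could record two events; someone applying section 9.3.1.1 would record one patient.

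With limits as low as 3 and 5, one extra count matters. In step 1, two patients would reach the limit of 3 if one of them were tallied twice. The treatment could then be declared too poorly tolerated under a rule whose error rates were never stated. In a single-arm, unblinded trial the unit cannot be settled neutrally once the events are known.

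**Working it through.** **Inputs.** Patients: 14, then 17 more, 31 in all (4.2, 9.3.1.1). Acceptable rates: 7% at 25 mg and 10% at 50 mg. Unacceptable rates: 15% and 20% (4.2). Limits: 3 in step 1 (4.2), 5 cumulatively at 25 mg and 5 at 50 mg (both sections). Step 3 is taken as a fresh count with 31 patients at risk, as section 9.3.1.1 words it.

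**1. The plan's own figures, one count per patient.** With X1 ~ Bin(14, p), X2 ~ Bin(17, p) and X3 ~ Bin(31, q):

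P(stop) = 1 − P(X1 ≤ 2 and X1 + X2 ≤ 4) × P(X3 ≤ 4)

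- At 7% and 10%: 1 − 0.8971 × 0.8068 = 0.2762. Stated: 27.6%.
- At 15% and 20%: 1 − 0.4359 × 0.2287 = 0.9003. Stated: 90.0%.

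Both figures reproduce, so the design was calculated on patients.

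**2. The step 1 limit printed in section 9.3.1.1.** Replacing X1 ≤ 2 by X1 ≤ 3:

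- At 7% and 10%: 1 − 0.9344 × 0.8068 = 0.246.
- At 15% and 20%: 1 − 0.4878 × 0.2287 = 0.888.

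The stated error rates therefore belong to the limit of 3 in section 4.2, not to the limit of 4 printed beside them.

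**3. Literal event counting.** Let d be the share of failing patients who meet two criteria at the same assessment and are tallied twice. The protocol gives no value, so d is an assumption. Each patient contributes 0, 1 or 2 events with probability 1 − p, p(1 − d) and pd. The total is the exact convolution over patients, with limits 3, 5 and 5.

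| d | Pass steps 1–2 (7%) | Pass step 3 (10%) | Wrong stopping | Detection (15%/20%) |
|---|---|---|---|---|
| 0% | 0.8971 | 0.8068 | 27.6% | 90.0% |
| 5% | 0.8689 | 0.7712 | 33.0% | 91.8% |
| 10% | 0.8420 | 0.7373 | 37.9% | 93.2% |
| 20% | 0.7919 | 0.6743 | 46.6% | 95.4% |

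Wrong stopping is 1 minus the product of the two pass probabilities; for d = 10%, 1 − 0.8420 × 0.7373 = 0.379. In step 1 alone it rises from 7.0% to 10.5% (d = 10%) and 13.7% (d = 20%).

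**4. Sensitivity to who is at risk in step 3.** Leavers do not return (4.6) and replacement is not applicable (5.3.3). With only the remaining patients at risk and a step 1 limit of 3, wrong stopping is 24.7% at d = 0, 30.1% at 5% and 35.0% at 10%. With the limit of 4 as well, d = 5% gives 26.5%.

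**The case against.** A reader might infer that the protocol makes a patient with two criteria count twice, and hence that 27.6% is understated. The documents do not support this. No section says that such a patient is two events. What section 4.2 counts is an event that requires termination, and a patient's treatment can be terminated only once. Permanent exit on at least one criterion points to one count per patient, as does section 4.2's framing of its hypotheses as frequencies of intolerance. Section 4.2 also quotes a 27% risk beside its own rules, which fits patient counting. For that unit, 27.6% is correct.

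The opportunity for simultaneous criteria is also limited. Of nine potassium measurements after baseline in a step, six fall on days with no scheduled creatinine or blood pressure (seven for group A in step 2). The value of d is assumed throughout. Under the step 3 and step 1 variants in the last check, a small d can leave the risk below 27.6%. And event counting raises detection, so its effect is not purely harmful.

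A reader might also infer that a single patient could end the trial in step 1. That would need three criteria met at once and each tallied. The calculation allows at most two events per patient, and the protocol gives no basis for a probability of three.

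All of this stands against the stronger claim. It leaves the two units in place: patient counting is the likelier intention, but the operative section does not say so, and the double tally at one assessment is not excluded.

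**Conclusion.** The mismatch is real and lies in the trial's decision rule, but it is a defect of wording, not an error in the 27.6%. The stated 27.6% and 90.0% are right for one count per patient, limits of 3 of 14, 5 of 31 and 5 of 31, and 31 patients at risk in step 3. They would not describe a rule that counted events literally: with 5% to 20% of failing patients tallied twice, wrong stopping would lie between 33.0% and 46.6%, and detection between 91.8% and 95.4%. That range depends wholly on an assumed share and shows only how sensitive the rule is to its unit.

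The conflict over the step 1 limit needs no assumption. The two sections print different numbers, and only the limit in section 4.2 returns the stated error rates. The points belong together, because settling one would leave the rule ambiguous on the other.

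**What to change.** In section 4.2, steps 1, 2 and 3, express each limit as the number of patients with at least one adverse event requiring termination of treatment, each patient counted once. Keep every criterion that such a patient meets in the descriptive breakdown of section 9.1, so that no safety information is lost. If a count of events is really intended, say so and recompute both error rates for it.

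In the same edit, reconcile the step 1 limit between sections 4.2 and 9.3.1.1 and print the error rates that belong to the limit kept: 27.6% and 90.0% for 3, or 24.6% and 88.8% for 4, both with 31 patients at risk in step 3. Which limit applies is for the sponsor to decide.

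The cost is a few sentences of wording. It needs no extra patients, visits or data, and the unit change alters no clinical criterion.

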### **2.4. Description and justification for the route of administration, the dose, the administration scheme and the duration of experimental treatments**

Eplerenone was granted MA for oral administration after the EPHEUS study (Pitt *et al.*, 2003) which demonstrated its efficacy in heart failure. It is administered daily as one dose.

In this tolerance study, we wish to investigate increasing doses of the two commercially available preparations (25 and 50 mg) in order to determine the therapeutic window between the minimal effective dose and the maximum tolerated dose (limiting this to a maximum of 50 mg/day) in renal transplant patients receiving CsA.

In a Spanish study in 11 patients (Gonzalez Monte *et al.*, 2010), 25 mg spironolactone achieved the primary objective of efficacy (proteinuria) in 3 months. The effect on kalaemia was maximal from the first month of treatment. We therefore think that we will see an increase in kalaemia in the first weeks of treatment (which will be maximal at the 4th week) and other adverse events in the following weeks: for this reason, we will carry out steps of 8 weeks (2 months).

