#### **4.5. Anticipated duration of participation of subjects and description of the chronology and duration of all periods of the study (including follow-up)**

##### **4.5.1 Expected duration of participation of subjects**

The maximum participation of patients taking part in the study in group A will be 3 steps of 8 weeks, thus 24 weeks in total.

The maximum participation of patients taking part in the study in group B will be the 2 final steps of 8 weeks (2 and 3), thus 16 weeks in total.

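### The step-2 stop counts adverse events within one 8-week window in section 4.2 but patients out of 31 in section 9.3.1.1, and the stated error rates hold only for a cumulative count of patients.

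*Protocol*

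**What the plan says.** Section 4.2 describes a Simon-type two-stage plan at 25 mg/day followed by a single evaluation at 50 mg/day. For step 2, 17 patients join the first 14, all are treated for 8 weeks, and the rule is: "If >4 adverse events requiring the termination of treatment occur during the 8 weeks, the study will be stopped". The unit is the adverse event and the window is step 2.

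Section 9.3.1.1 gives the same decision in patients. At 5 or more, "patients out of the 31 have a limiting toxicity, the alternative hypothesis can be rejected and the study will be stopped". The unit is the patient and the denominator is everyone enrolled.

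Other sections bear on the count:

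- Sections 4.6 and 4.6.1: participation ends at an event that requires eplerenone to be stopped, and re-entry is not possible.
- Section 5.3.1: a patient leaves on meeting one or more of the listed criteria.
- Section 5.3.3: replacement of subjects is not applicable.
- Section 4.5.1: the maximum participation for "group A will be 3 steps of 8 weeks, thus 24 weeks in total". The first two of those steps are at 25 mg, so group A has 16 weeks at that dose and group B has 8.
- Section 2.4, on an earlier spironolactone study: "The effect on kalaemia was maximal from the first month of treatment". The same paragraph expects other adverse events in later weeks.

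The design rates in 4.2 are an acceptable level at which "the frequency of intolerance to treatment is <7% for a dose of 25 mg/day and <10% for a dose of 50 mg/day" and an unacceptable level at which "its use does not appear possible if the respective frequencies are >15% and 20%, respectively". Section 9.3.1.1 ties the acceptable rates to 8 weeks of treatment. It claims that "the probability of demonstrating a limiting toxicity greater than the fixed norms is 90.0%, the risk of stopping the study wrongly is 27.6" percent. Section 4.2 adds: "There is a 60% chance of interrupting the study before the increase in dose if the hypothesis of unfavourable treatment is correct".

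**The concern.** A binomial stopping rule needs one yes/no outcome per patient over a defined exposure. The two sections disagree on both the unit and the window.

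- **Window.** Up to 2 patients can fail in step 1 and the trial still proceeds. They cannot be among those treated in step 2, so the literal 4.2 count omits them.
- **Unit.** If one patient meets, for example, the potassium and creatinine criteria at the same exit, 4.2 does not say whether that is one event or two.
- **Exposure.** If the count is instead cumulative over steps 1 and 2, group A brings 16 weeks at 25 mg against rates set for 8.
- **Hypothesis wording.** In 9.3.1.1 the alternative is the unacceptable rate, yet 5 or more failures out of 31 is said to reject it. The same paragraph also rejects it when 4 or fewer fail at 50 mg.

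What is at stake is the decision to escalate the dose. It can depend on which section is followed, and the error rates quoted to justify 31 patients may not belong to the rule that is applied.

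**Working it through.** **Inputs.** n₁ = 14 and n₂ = 17 (4.2); (p₂₅, p₅₀) = (0.07, 0.10) acceptable and (0.15, 0.20) unacceptable (4.2, 9.3.1.1); step-2 limit 4 and step-3 limit 4 (both sections); step-1 stop at 3 (4.2) or 4 (9.3.1.1); 31 patients in step 3 (9.3.1.1); no loss to follow-up (9.3.1.5). Below, b is the binomial probability and B the cumulative probability.

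**1. Reproduce the stated figures.** Count each patient once, cumulatively, with step-1 cut-off 3:

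P(escalate) = Σ b(x₁; 14, p₂₅) · B(4 − x₁; 17, p₂₅), for x₁ = 0, 1, 2.

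- At 15%: 0.1028×0.9013 + 0.2539×0.7556 + 0.2912×0.5198 = 0.4359, so stopping before escalation is 56.4%. With B(4; 31, 0.20) = 0.2287, detection = 1 − 0.4359×0.2287 = 0.9003.
- At 7%: 0.3620×0.9949 + 0.3815×0.9727 + 0.1867×0.8882 = 0.8971. With B(4; 31, 0.10) = 0.8068, wrong stopping = 1 − 0.8971×0.8068 = 0.2762.

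This matches 90.0% and 27.6%. None of the other rules tried matches both: step-1 cut-off 4 gives 88.8% and 24.6%; only the remaining patients in step 3 gives 86.3% and 24.7%; the step-2-only counts are below. The stated 60% is not reproduced (56.4%), so 56.4% is the baseline used here.

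**2. Literal 4.2 count, no further group A events.** P(escalate) = B(2; 14, p₂₅) · B(4; 17, p₂₅).

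- At 15%: 0.6479×0.9013 = 0.5840. Early stopping is 41.6%; detection = 1 − 0.5840×0.2287 = 86.6%.
- At 7%: 0.9302×0.9949 = 0.9255. Wrong stopping = 1 − 0.9255×0.8068 = 25.3%.
- The two counts reach opposite decisions with probability 0.5840 − 0.4359 = 14.8% at 15%, and 0.9255 − 0.8971 = 2.8% at 7%.
- With only the remaining patients in step 3, detection goes from 86.3% to 80.5%.

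**3. Literal 4.2 count, group A's same 8-week risk recurs (assumption).** P(escalate) = Σ b(x₁; 14, p₂₅) · B(4; 31 − x₁, p₂₅), for x₁ = 0, 1, 2.

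- At 15%: 0.3457. Early stopping is 65.4%; detection = 1 − 0.3457×0.2287 = 92.1%.
- At 7%: 0.8775. Wrong stopping = 1 − 0.8775×0.8068 = 29.2%.

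**4. Cumulative count including group A's second 8 weeks.** Let q be the assumed risk in those weeks. At 7%, P(escalate) is 0.8511 for q = 3.5% and 0.7866 for q = 7%. Multiplying by 0.8068 gives wrong stopping of 31.3% and 36.5%, against 27.6%. Detection rises as well: at 15%, q from 3.5% to 15% gives 91.6% to 95.9%.

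**5. Several criteria at one exit (assumption).** Suppose 10% to 30% of failing patients meet two criteria at once, each tallied, under the cumulative count with cut-off 3. Stopping at 25 mg then rises from 10.3% to 15.8%–25.4% at the 7% rate, and from 56.4% to 63.3%–73.8% at the 15% rate.

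**The case against.** The intended rule can be inferred. Section 4.2 invokes Simon's plan and names 14+17 patients; since failures neither return nor are replaced, that total fits a count from enrolment. More than 4 is the same limit as 5 or more, and the cumulative patient count recovers the stated figures. Figure 1, which 4.6 cites for the withdrawal rules, is not visible here. This supports treating the matter as a correction of wording. It does not remove the conflict, because a reader applying 4.2 as written would use a different count.

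Four stronger readings are tempting, and the documents do not support them:

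- **That detection falls from 90% to 80.5% because of the counting rule.** That contrast also changes the step-3 denominator, a separate matter. Like for like, the loss is 3.4 points (90.0% to 86.6%) or 5.8 points (86.3% to 80.5%).
- **That the literal rule always stops too rarely.** Direction depends on group A's risk in weeks 9–16. Section 2.4 expects the potassium effect early but other events later, so the no-event and full-recurrence cases serve as two reference points.
- **That one patient can be counted repeatedly over time.** Exit at a terminating event, without re-entry, rules this out. Only several criteria at the same exit remain open.
- **That 10 of 31 failures with an acceptable verdict (2+4+4) measures the defect.** The cumulative design already allows 4+4 = 8; the wording adds at most 2.

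The inverted hypothesis is a wording slip: the action attached to it, stopping, is clear, so no decision changes.

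**Conclusion.** The point stands as a contradiction in a decision threshold. Sections 4.2 and 9.3.1.1 differ in unit and window, and the literal 4.2 rule does not have the stated operating characteristics. Neither section alone states the rule that does, because the matching step-1 cut-off is in 4.2 and the matching count of patients is in 9.3.1.1.

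With 31 patients in step 3 and true rates of 15% and 20%, the literal rule gives early stopping between 41.6% and 65.4% and detection between 86.6% and 92.1%. The ends correspond to no group A risk and full recurrence in weeks 9–16. The comparators are 56.4% and 90.0%. These results assume independent patients and complete follow-up. The recurrence risks and the share of patients with concurrent criteria are assumptions; the protocol gives neither.

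**What to change.** 1. In section 4.2, express the rules as patients with at least one event that requires treatment to be stopped, each patient counted once. State that step-1 failures carry forward into the step-2 count out of 31.
2. Reconcile 4.2 and 9.3.1.1 on whether group A's events in weeks 9–16 at 25 mg count towards the stop. The documents do not settle this, and leaving those events out would itself be a new stopping rule, so the sponsor must decide and say so.
3. Restate the error rates, including the 60% figure, for the rule adopted. This requires the step-1 cut-off (3 in 4.2, 4 in 9.3.1.1) and the step-3 denominator to be reconciled as well.
4. Correct the hypothesis wording in 9.3.1.1, so that 5 or more of 31 is no longer said to reject the unacceptable-rate hypothesis.

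The cost is a few sentences and a short exact binomial calculation. No new data or visits are needed.

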### **Clinical and biological surveillance (Tables 1 and 2)**

Clinical surveillance for group A:

- Step 1: D0, D14, D28 and D56.
- Step 2: D0 (D56 of step 1), D28 (84th day of participation) and D56 (112th day of participation)
- Step 3 (change of dose): D0 (D56 of step 2), D14 (126th day of participation), D28 (140th day of participation) and D56 (168th day of participation).

Clinical surveillance for group B:

- Step 2: D0, D14, D28 and D56.
- Step 3 (change of dose): D0 (D56 of step 2), D14 (70th day of participation), D28 (84th day of participation) and D56 (112th day of participation).

Biological surveillance: blood samples on D0, D2, then weekly until the end of this step for kalaemia, blood samples on D0, D14, D28 and then every month for creatinaemia and urine samples on D0 and then every month for creatininuria, blood inogram and proteinuria.

The specimens for the measurement of kalaemia should be taken without a tourniquet.

Monitoring of kalaemia 48 hours after the initiation of treatment (D2) then every 7 days until the end of the study. Consultation with an investigator, in addition to the planned schedule, if necessary (appearance of an adverse event).

The specimens at inclusion, during consultations and at the end of the study will be taken at the Nephrology Service Day Hospital (NSDH) of the CHU, Reims. The specimens for surveillance of kalaemia will be taken at the usual Medical Analysis Laboratory (MAL) used by patient. An agreement will link the investigational centre and the MAL. The result for kalaemia will be faxed to the CRICAM ([contact]), and the investigational physician will be informed of the result on the same day).

Two groups will be distinguished:

- Group A will comprise patients who start the study on the first day of the study; there will be 14 at inclusion
- Group B will consist of patients who start the study directly at step 2; there will be 17 who will be included specifically

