#### **4.6. Rules for permanent or temporary withdrawal from the study**

See Figure 1 and section 4.2

Withdrawal from the study is permanent: a patient who has left the study cannot re-enter the study.

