##### **4.6.1 For participation of a patient in the study**

The participation of a patient finishes either at the end of the study (end of step 3) or after the development of an adverse event requiring the premature termination of eplerenone in this patient.

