##### **4.6.2 For all or part of the study**

The end of the study will either be at the end of step 3 or after the development of a large number of adverse events requiring the premature termination of eplerenone in the patients as defined in section 4.2.

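### The step-2 stopping rule in section 4.2, as worded, leaves out step-1 failures, so it can contradict section 9.3.1.1 on whether to raise the dose to 50 mg/day

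*Protocol*

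**What the plan says.** Section 4.2 treats 14 patients at 25 mg/day for 8 weeks (step 1) and stops at 3 or more terminating events. Otherwise 17 patients are added and all are treated for a further 8 weeks (step 2). The study then stops "If >4 adverse events requiring the termination of treatment occur during the 8 weeks"; with 4 or fewer it goes to step 3, which is "an increase in the dose of eplerenone to 50 mg/day in all patients who participated in step 2".

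Section 9.3.1.1 gives the step-2 rule differently: stop if 5 or more "patients out of the 31 have a limiting toxicity"; otherwise "the dose will be increased to 50 mg for 31 patients".

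Three other places fix how 4.2 works:

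- The surveillance schedule makes step 2 a separate window for group A: "Step 2: D0 (D56 of step 1").
- Section 4.6 says "Withdrawal from the study is permanent: a patient who has left the study cannot re-enter the study", and under 4.6.1 participation ends "after the development of an adverse event requiring the premature termination of eplerenone in this patient". Section 5.3.3 makes replacement not applicable.
- Section 4.6.2 ends the study after a large number of "adverse events requiring the premature termination of eplerenone in the patients as defined in section 4.2". The operative stopping rule is therefore the one in 4.2.

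Section 9.3.1.1 states a 90.0% chance of detecting excess toxicity and a 27.6% risk of stopping wrongly. Section 4.2 states a 60% chance of stopping before the dose increase if the unfavourable hypothesis is true.

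**The concern.** The same data should give one answer at the gate between 25 and 50 mg/day. Here they can give two. A patient who fails in step 1 has left for good and cannot have an event in step 2's window, so 4.2 read literally drops that failure. Section 9.3.1.1 counts over everyone enrolled.

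At stake is doubling the dose in patients for whom, by the protocol's own account in section 2.6, eplerenone is contraindicated on two grounds (renal function and cyclosporine). Under the 4.2 wording escalation is possible after 2 + 4 = 6 of 31 failures at 25 mg (19.4%). That is above the 15% that the protocol calls unusable. Section 9.3.1.1 allows at most 4 (12.9%).

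**Working it through.** **Inputs from the protocol.** 14 patients in group A and 17 in group B; step-1 stop at 3 or more of 14 (section 4.2); step-2 limit of 4; step-3 limit of 4 at 50 mg; acceptable rates 7% (25 mg) and 10% (50 mg); unacceptable rates 15% and 20%.

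**Assumption not in the protocol.** h is the risk that a group A patient still on treatment fails in the second 8 weeks at 25 mg. It is taken from zero to the full 8-week rate.

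**Notation.** x ~ Bin(14, p25) is step-1 failures, y ~ Bin(17, p25) group B failures in step 2, and z ~ Bin(14 − x, h) group A failures in step 2. Step 2 is reached if x ≤ 2.

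- 4.2 as worded escalates if y + z ≤ 4.
- 9.3.1.1, each patient's first 8 weeks: escalates if x + y ≤ 4.
- 9.3.1.1, all time at 25 mg: escalates if x + y + z ≤ 4.

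**Reproducing the stated figures** (first-8-week count, 31 patients at 50 mg).

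P(escalate) = Σ over x = 0, 1, 2 of P(x) · P(y ≤ 4 − x).

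- At 15%: 0.0926 + 0.1919 + 0.1514 = 0.4359. Early stop = 1 − 0.4359 = 56.4%, against the stated 60%. P(Bin(31, 0.20) ≤ 4) = 0.2287, so detection = 1 − 0.4359 × 0.2287 = 90.03%.
- At 7%: 0.3602 + 0.3711 + 0.1658 = 0.8971. P(Bin(31, 0.10) ≤ 4) = 0.8068, so wrong stop = 1 − 0.8971 × 0.8068 = 27.62%.

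Both match the stated 90.0% and 27.6%. With the step-1 limit of 4 that 9.3.1.1 prints, the same sum gives 88.8% and 24.6%. The stated pair therefore belongs to the limit of 3; that discrepancy is a separate matter.

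**Opposite decisions.** Step 1 + step 2 failures of 2 + 3, 1 + 4 or 2 + 4 total 5 or 6 of 31, so 9.3.1.1 stops, while 4.2 sees 3 or 4 and escalates. On the first-8-week count this requires the step-2 failures to be in group B; on the all-time count they may be in either group.

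**How often.** At h = 0 and a true 15%, the disagreement is P(x=1)·P(y=4) + P(x=2)·P(y=3 or 4) = 0.0370 + 0.1111 = 14.8%. Over the range of h:

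| Comparison | True rate | h = 0 | h = half rate | h = full rate |
|---|---|---|---|---|
| First-8-week count: 4.2 escalates, 9.3.1.1 stops | 15% | 14.8% | 8.3% | 4.1% |
| First-8-week count: 4.2 stops, 9.3.1.1 escalates | 15% | 0% | 4.5% | 13.1% |
| First-8-week count: 4.2 escalates, 9.3.1.1 stops | 7% | 2.8% | 2.3% | 1.8% |
| First-8-week count: 4.2 stops, 9.3.1.1 escalates | 7% | 0% | 1.1% | 3.7% |
| All-time count: 4.2 escalates, 9.3.1.1 stops | 15% | 14.8% | 17.8% | 16.4% |
| All-time count: 4.2 escalates, 9.3.1.1 stops | 7% | 2.8% | 5.8% | 9.1% |

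On the all-time count the reverse disagreement is impossible, because x + y + z ≤ 4 implies y + z ≤ 4.

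**Overall rates of the 4.2 wording** (31 patients at 50 mg, h from zero to full): detection 86.6% to 92.1%, wrong stop 25.3% to 29.2%, early stop at 15% 41.6% to 65.4%.

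**The case against.** The strongest reply is that this is loose wording of a recoverable rule. Section 4.2 calls steps 1 and 2 a Simon two-stage plan, whose second-stage count is cumulative. It refers to the patients as 14+17, although after any step-1 failure fewer than 31 remain on treatment. The stated error rates come out to the decimal under a cumulative count. Figure 1, part of 4.2, may show the cumulative count outright. Patients are also protected by individual stopping criteria, by potassium checks at D2 and then weekly, and by an independent committee that sees all files.

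Much of this stands. A cumulative count was probably meant, and the missing figure limits how firmly anyone can say that 4.2 as a whole is wrong. But the sentence that governs stopping ties the count to step 2's weeks, nothing in the text carries step-1 failures forward, and 4.6.2 points to that section. The individual safeguards do not tell the team whether the study passes the gate.

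Two stronger readings are tempting and should be resisted. A reader might infer that every disagreement is an unsafe escalation. That holds only if 9.3.1.1 also counts group A's second 8 weeks, which it does not say; on the count that reproduces the stated rates, 4.2 can be the stricter rule. A reader might also infer that the design loses power. The ranges for the 4.2 wording lie on both sides of 90.0% and 27.6%, so the documents support no fixed loss.

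**Conclusion.** The contradiction is real in the text. Sections 4.2 and 9.3.1.1 can give opposite decisions on escalation from the same data, and 4.2 as worded permits 50 mg/day after 6 of 31 failures at 25 mg.

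The conflict in the rules does not depend on h, but its frequency does. At a true 15%, on the first-8-week count, wrong escalation runs from 14.8% at h = 0 down to 4.1% at the full rate, and the reverse disagreement rises from 0% to 13.1%. If all time at 25 mg counts, every disagreement is toward escalation, at 14.8% to 17.8%. All these figures use the step-1 limit of 3.

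The finding is about the wording, subject to what Figure 1 shows. It does not show that the sponsor intended to discard step-1 failures.

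**What to change.** State in 4.2, and in the same words in 9.3.1.1, that the study stops before 50 mg/day if 5 or more of the 31 enrolled patients have had a terminating event at 25 mg/day, step-1 failures included. Say which weeks count, and check that Figure 1 agrees.

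- **Minimal option:** count each patient over the first 8 weeks at 25 mg. This keeps the stated 27.6% and 90.0%, which assume 31 patients at 50 mg. Restate the 60% chance of early stopping as about 56%. The cost is one sentence in each section and one corrected figure, with no added patients or visits.
- **Optional extension:** also count group A's second 8 weeks. The rates (31 patients at 50 mg) then become 27.6% to 36.5% wrong stop, 90.0% to 95.8% detection and 56% to 82% early stop, depending on h. The downside is up to 36.5 − 27.6 = 8.9 percentage points more wrong stopping. This is a choice for the sponsor and is not needed to reconcile the two sections.
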